**Aim of the project**

The function of frataxin is still unknown, but strong evidence supports the concept that is critically involved in mitochondrial function and oxidative metabolism. Our previous studies demonstrate increase of frataxin-levels in lymphocytes of FRDA patients after rhuEPO administration. However, the pathological cascade in FRDA is not exquisite to the central nervous system, but also involves peripheral nerves and skeletal muscle. We therefore intent to investigate effects of rhEPO on circulating and intramuscular endothelial progenitor cells, neovascularization and oxidative metabolism of skeletal muscle in FRDA.

Numbers of circulating CD34 and CD133 hematopoietic progenitor cells will be measured in the peripheral blood by FACS analysis at baseline and bi-weekly throughout the study phase. Muscle biopsy will be performed at baseline and after two months rhuEPO treatment to study effects of EPO on Frataxin expression, numbers of CD34 and CD133 hematopoietic progenitor cells, satellite cells, capillary density and respiratory chain complex activities.

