**Study Design**

This is a single centre, non randomized pilot study.

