**Patients and Investigations**

Seven adult subjects with definite FRDA will be enroled in this study. Skeletal muscle will be obtained by an open biopsy from at baseline (untreated) and after 2 months of rhuEPO treatment after written informed consent.

Treatment encompasses rhuEPO 3.000 IU (~100 IU/kg KG) three times weekly subcutaneously for 8 weeks.

Specimen from the quadriceps muscle and MR spectroscopy from the contralateral side will be obtained pre- and post rhuEPO treatment.

Frataxin-levels will be assessed in lymphocytes and muscle specimen at baseline and study end-point. Furthermore, FACS analysis of circulating CD34+ and CD133+ cells in peripheral blood will be perfomed bi-weekly. The numbers of CD34+ and CD133+ cells and capillary density per mm2 will be quantified in skeletal muscle at baseline and after 8 weeks EPO treatment.

Biochemically, complex I, II, and III of the respiratory chain in the quadriceps muscle will be evaluated pre-and post treatment.

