**Statistical analysis**

Depending on the distribution of variables (analyzed by the Kolmogorov-Smirnov test) parametric (i.e. one-way analysis of variance (ANOVA); Pearson’s correlation coefficient for univariate correlation analyses) or non-parametric tests (Kruskal-Wallis test; Mann-Whitney-U test for group comparisons, Spearman’s correlation coefficient for univariate correlation analyses) will be used. Multivariable linear regression analysis, controlling for possible confounding covariates, will be performed for the variables found to be significant in the univariate models. Categorial variables will be analysed by chi-square test and logistic regression analysis.

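### The comparison tests that the protocol names assume independent groups, but the treatment aims are before/after comparisons within one treated group of 5 to 7 patients, and no paired or repeated-measures method is named

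*Protocol*

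**What the plan says.** The Study Design section reads "This is a single centre, non randomized pilot study". No control or comparison group is described anywhere. Number of patients gives a range of 5 to 7; Patients and Investigations says "Seven adult subjects with definite FRDA will be enroled in this study". All receive the same drug on one schedule.

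The treatment questions are put to the same patients at different times:

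- Aim of the project: "Muscle biopsy will be performed at baseline and after two months rhuEPO treatment to study effects of EPO on Frataxin expression". Circulating progenitor cells are measured "by FACS analysis at baseline and bi-weekly throughout the study phase".
- Patients and Investigations: "Specimen from the quadriceps muscle and MR spectroscopy from the contralateral side will be obtained pre- and post rhuEPO treatment" and "Frataxin-levels will be assessed in lymphocytes and muscle specimen at baseline and study end-point".
- The visit table under Synopsis repeats SARA and FACS at several visits.

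Statistical analysis is the only section on hypothesis tests. The parametric comparison is one-way ANOVA, introduced by i.e., so it is specified and not offered as an example. The non-parametric choice is "Kruskal-Wallis test; Mann-Whitney-U test for group comparisons". The section adds Pearson and Spearman correlation, multivariable linear regression and, for categorical variables, chi-square and logistic regression. It names no paired t test, signed-rank test, Friedman test, repeated-measures ANOVA, mixed model or McNemar test, and does not say which groups are to be compared.

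**The concern.** One-way ANOVA, Kruskal-Wallis and Mann-Whitney U require the values in each group to come from different, unrelated subjects. Here the only groups that could be formed for a treatment effect are visits of the same patients. An unpaired test then uses the wrong variance for the mean change: it ignores the covariance between a patient's two values. If patients who start high tend to stay high, the test is too conservative and real changes can be missed. If the correlation is negative, it rejects too often.

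The frataxin, progenitor-cell, satellite-cell, capillary, respiratory-chain and spectroscopy comparisons all have this structure. With at most seven patients, each undergoing two open biopsies, the before/after structure may be the main source of precision, and the written plan does not use it.

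**Working it through.** The protocol states no alpha, power, effect size or SD, so it has no figure to reproduce. The check is a comparison of the named tests with the design, followed by a calculation of what the mismatch could cost.

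**Inputs**
- From the protocol: one treated group, n from 5 to 7, values at week 0 and week 8 in the same patients.
- Assumed, because the protocol gives none: two-sided alpha 0.05, normal data with equal SD σ at both times, a shift of 0.8σ, and within-patient correlation ρ from 0 to 0.9 (plus −0.3 for the direction of the error).

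**Standard error of the mean change**
- Used by an unpaired test: σ·√(2/n).
- Correct for paired data: σ·√(2(1−ρ)/n).
- Ratio: 1/√(1−ρ), which is 1.00 at ρ=0, 1.20 at 0.3, 1.41 at 0.5, 1.83 at 0.7, 3.16 at 0.9, and 1/√1.3 = 0.88 at −0.3.

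Example with n=7 and ρ=0.7: √(2/7) = 0.535σ against √(0.6/7) = 0.293σ, and 0.535/0.293 = 1.83.

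**Power for a shift of 0.8σ**

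Paired t: noncentral t on n−1 degrees of freedom with noncentrality 0.8·√(n/(2(1−ρ))). At n=7 and ρ=0.7 this is 0.8·√(7/0.6) = 2.73 against a critical value of 2.45 on 6 df, giving 63%. Unpaired t (the same test as one-way ANOVA with two groups): simulation of correlated normal pairs.

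| ρ | n=7 unpaired | n=7 paired | n=5 unpaired | n=5 paired |
|---|---|---|---|---|
| 0 | 28% | 24% | 20% | 17% |
| 0.3 | 25% | 33% | 17% | 22% |
| 0.5 | 23% | 43% | 15% | 28% |
| 0.7 | 21% | 63% | 14% | 42% |
| 0.9 | 18% | 97% | 12% | 84% |

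Entries are rounded; smaller simulation runs differ by about one percentage point. At ρ=0 the paired test is slightly worse because it has 6 degrees of freedom instead of 12 (critical value 2.45 against 2.18).

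**Actual type I error of the named tests, n=7, nominal 5%**

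| ρ | One-way ANOVA | Mann-Whitney U |
|---|---|---|
| −0.3 | 8.2% | 6.4% |
| 0 | 5% | 3.7% |
| 0.3 | 2.4% | 1.8% |
| 0.5 | 1.2% | 1.0% |
| 0.7 | 0.3% | 0.2% |
| 0.9 | about 0.01% | about 0.01% |

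The paired t test holds about 5% throughout.

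**Serial values.** For five occasions, n=7 and equal correlation between all of them, the type I error of Kruskal-Wallis / one-way ANOVA is 0.5% / 0.6% at ρ=0.5 and 0.04% / 0.12% at ρ=0.7. Friedman stays near 3.9%. For a linear rise of 0.8 SD at ρ=0.7, power is about 6 to 7% for one-way ANOVA and 57 to 59% for a repeated-measures analysis.

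**Limit of the rank-based alternative.** The smallest exact two-sided signed-rank p is 2/2ⁿ: 0.0625 at n=5, 0.031 at n=6 and 0.016 at n=7. At n=5 that test cannot reach 0.05 whatever the data.

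**The case against.** The section never says that these tests will be applied to week 0 versus week 8. It refers to group comparisons and defines no groups. Aim 1 is a baseline description, for which the listed correlations are suitable, and a separate analysis plan might name the before/after test. It is therefore fair to say that the named tests do not fit the design. A reader might go further and infer that the sponsor will certainly discard the pairing; the text does not settle that. But the baseline-only reading does not rescue the section: no second group is described for aim 1 either, and aims 2 to 4 would then have no test. The section also fixes its methods rather than deferring them, so a later plan would either inherit the mismatch or contradict the protocol.

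A reader might infer that between-patient variance is bound to dominate, given the varied disease course described under Friedreich Ataxia (FRDA). That section covers onset, repeat length, cardiomyopathy and diabetes. It gives no variance for muscle cell counts, capillary density, enzyme activity or PCr kinetics. Counts over 1 mm² from two separate biopsies could correlate weakly, and near zero correlation pairing gains nothing.

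Three narrower points also stand. Not every listed method is an independent-group test, since correlation and regression are named too. The protocol promises no confidence intervals, so it cannot be said to plan intervals that are too wide. And in a pilot with no stated alpha or power, an error that is conservative under positive correlation can be repaired later from the same data, although fixing the method before the results are seen is better.

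**Conclusion.** The point holds. Every comparison test named assumes independent observations, chi-square and logistic regression do too, and nothing listed accounts for pairing, while aims 2 to 4 are within-patient comparisons in one treated group. Applied to those aims, the tests give incorrect p values and standard errors of the change. This is an error in what is written, not a detail left for later.

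The size is not fixed by the document. Under the stated assumptions, the change in power at n=7 from using the paired analysis runs from a loss of about 4 points at correlation 0 (28% to 24%) to a gain of about 79 points at 0.9 (18% to 97%). At n=5 it runs from a loss of about 3 points to a gain of about 72. The large gains belong to the upper part of the correlation range.

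A reader might infer that the mismatch produces false positive findings. With positive correlation it does the opposite: type I error falls below nominal and effects are missed. Only a negative correlation would inflate false positives.

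**What to change.** In Statistical analysis, replace the group tests for treatment effects with the following.

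- **Week 0 versus week 8:** analyse the within-patient change and report the estimate with a 95% CI from a paired t analysis. Use the log ratio where all values are positive. Where counts can be zero, use the raw difference or an offset stated in advance.
- **Sensitivity:** exact Wilcoxon signed-rank, with a note that its two-sided p cannot fall below 0.0625 if only five patients contribute. The estimate and interval should therefore lead.
- **Serial FACS and SARA:** a mixed model with a patient random intercept and a small-sample degrees-of-freedom correction, or the Friedman test.
- **Paired binary data, if any:** McNemar or another exact paired test in place of chi-square and ordinary logistic regression.
- Correlations may stay for the baseline aim. If any independent-group test is kept, say which groups it compares.

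The cost is a few sentences, with no extra patients, visits or samples. The one statistical price is a slight loss of degrees of freedom if the within-patient correlation is near zero.

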**Interventions**

**Treatment**

Human recombinant erythropoietin (rhuErypo) will be applyed three times weekly. The dosage will be 3.00 IU Neo-Recormon (Roche). The appication of the medication will be done by the patient in the gluteal area: In case of iron deficiency (anemia) Fe will be substituted. (z.B. 200 mg elementares Eisen/Tag).

**Hemoglobin/Modification of dosage**

In case of increase in Hämoglobin values >185 g/l in male patients (Grenzwert 130-177 g/l) und >165 g/l (Grenzwert 120-157 g/l) in female patients Phlebotomy will be performed (150 -200 ml).

